### Secondary outcomes

Secondary outcomes will measure physical function, frailty and nutritional status, pain and self-reported health status using a broad test battery outlined in Table 2.

**Table 2 pone.0300412.t002:** Test battery.

Construct Measured	Test
Sarcopenia and upper limb strength	Upper/Lower Limb circumference Hand grip dynamometry [27, 28]
Lower limb strength and endurance	30-sec Chair Stand Test [29]
Endurance and functional mobility	2-minute walk test [30]
Gait Speed	10m walk test [31]
Balance	Single leg stance [32]
Frailty	SHARE-FI [33], Clinical Frailty Scale [6]
Nutritional Status	Mini-Nutritional Assessment [34, 35]
Pain	Numerical Pain Rating Scale [36]
Health status/Quality of Life	Short Form 12 [37]

**1. Strength and muscular mass:** Muscle strength will be measured, using a Jamar Digital Hand Dynamometer, while sitting with the elbow flexed at 90°, the forearm mid-prone, the wrist in neutral and the hand unsupported [27, 28]. Results will be compared to normative reference values [38]. Two measurements will be recorded and also used for the SHARE-Frailty Instrument (FI) assessment [33].

Mid-calf circumference girth will be evaluated as this measure correlates with appendicular muscular mass [39]. This will be measured using a flexible tape measure at the level of the largest circumference of the calf. Measurements will be compared to gendered cut-off values [40]. Mid-arm muscle circumference reflects both muscle mass and caloric and protein adequacy and may be used to signify wasting or malnutrition [41]. This test has been recommended in situations where lower limb swelling is present [42]. The maximum upper arm muscular mass will be measured using a flexible tape measure. These results will be compared to global reference values [43].

**2. Physical performance and lower extremity physical function**:

This will be measured using the following physical performance measures:

The 10m Walk Test (10mWT). This test measures gait speed and functional mobility and is recorded in m/s. Gait speed is calculated as total distance/time [31].The 2 Minute Walk Test (2MWT). This test of self-paced walking ability and functional capacity assesses a participants’ ability to walk unaided over a 15m distance, as fast as possible, for two minutes. Rest breaks are permitted, and the distance covered is measured [30].The Chair Stand Test (CST). This tests lower limb strength and endurance and records the total number of sit to stand repetitions performed in 30 seconds [29].The Single Leg Stance Test (SLST). This balance test is performed on each leg. The participant is timed standing unassisted on one leg, with eyes open and hands placed on the hips [31].

**3. Frailty:** Frailty will be assessed using the Clinical Frailty Scale (CFS) [6] and the SHARE-Frailty Instrument (FI) [33]. The CFS is validated for people over 65 years. It is assessed by the tester. Each point on the scale correlates with a level of frailty and a visual chart aids classification from 1 (very fit) to 9 (terminally ill). Higher scores indicate higher levels of frailty. The SHARE-FI is validated for people over 50 years [33]. It consists of four brief questions related to the following variables: exhaustion, loss of appetite, walking difficulties and low physical activity, and grip strength measurement. The five results are entered into a freely available web calculator to generate a frailty score and a frailty category of non-frail, pre-frail and frail is also generated. A minor modification was made to the terminology of the SHARE-FI to reflect the real-world experiences of this population.

**4. Nutritional status** will be assessed using the Mini-nutritional assessment (MNA) which assesses the risk of malnutrition [34]. The short form of the MNA (MNA-SF) [35] is an efficient screening tool consisting of six questions on food intake, weight loss, mobility, psychological stress, or acute disease, the presence of dementia or depression, and body mass index (BMI). The maximum score for this part is equal to 14. A score of 12 or higher indicates a normal nutritional status thus excluding malnutrition and/or risk of malnutrition. The terminology of two of the questions of the MNA (regarding acuity of illness and psychological stress) were slightly modified for the purposes of evaluation of this population in this setting.

**5. Pain:** Each participant will be asked if they are experiencing pain and will be questioned about its location and duration. Pain severity will be assessed using the Numerical Rating Scale (NRS) [36]. The NRS is a unidimensional measure of pain intensity from 0–10, with 0 being zero pain and 10 the worst pain imaginable.

**6. Short-Form 12 (SF-12)** The SF-12 V2 is a self-report measure of health used across age, disease, and treatment groups [37]. It uses eight domains including physical and social activities, pain, mental health, emotional health, vitality and general health perceptions to measure health. The tester will read and complete the 12-question survey with the participant. Results will be entered into a software program provided by the licensing company QualityMetric and two summary scores, mental health (MCS12) and physical health (PCS12) will be generated.

The assessor will document any issues with terminology of the outcome measures utilised, difficulties with completion or floor or ceiling effects reached, as these instruments were designed with geriatric populations in mind.

Using a bespoke data collection form, the following demographic data will also be collected: age, gender, ethnicity, living arrangement and environment, highest level of education, marital status, employment status, history of incarceration, history of addiction, self-reported health, and medical history (S1 File and Fig 1).

**Fig 1 pone.0300412.g001:**
[figure not shown]
Spirit flow diagram.

#### Intervention

The intervention will involve a 10-week low threshold, trauma informed exercise intervention (including a twice weekly exercise class with protein supplementation and a once weekly outdoor ‘Park Walk’), delivered over 12 weeks to enable flexibility and maximum participation. An aim of this research approach is to enhance the programmes accessibility by providing flexibility and a level of awareness and understanding of past trauma, an approach which is recommended for people who have experienced chronic or complex trauma [44]. The LEAP-II trial, a linked study previously conducted a similar 12-week intervention [17]. While the results demonstrated evidence of effectiveness, the majority (91%) of those who attended regularly did not complete more than 10 weeks of the intervention. Behm et al (2023), proposed a minimal dose of once weekly multi-joint resistance training, with at least 6–15 repetitions using loads between 30–80% of one repetition maximum for 8–12 weeks to achieve a strengthening effect in untrained individuals [45]. Given that 10 weeks marks the midpoint of this finding, a pragmatic decision was made to shorten the duration of this feasibility study to prioritise and encourage increased retention and participation in this ‘hard to reach’ population who are known to engage poorly with mainstream services.

The intervention will be delivered by two research physiotherapists who will adhere to all safety procedures. Flexibility will be facilitated with the provision of a four-week window for pre-intervention evaluations prior to commencement of the programme. Using a trauma-informed lens [46] flexibly arranged group or one-to one sessions will be delivered based on participant preference. Exercise programming strategies and variables are based on our earlier work (LEAP-I and LEAP-II trials) [16, 17] and also informed by prior stakeholder involvement from people with lived experience. The exercise classes will be multi-modal, with a primary focus on strength and based on core set of resistance exercises (Table 3). Aerobic, balance and flexibility work will be integrated into the class and the exercises will be individualised based on initial assessment results and presentation of participants. Using a gender-based perspective, the following considerations and adaptions will be built into the class; (i) core-stability exercises to target pelvic floor and/or abdominal muscle weakness, (ii) bone building exercises to target peri-and postmenopausal bone loss and (iii) age-associated muscle mass loss. Music, dance and fun orientated physical activity games, an important feature of aforementioned linked studies, will be incorporated to optimize enjoyment and self-esteem. These features are incorporated to offer choice and enable empowerment in respect of a trauma informed approach, while carefully considering the exercise prescription parameters outlined above [45]. Borg’s Rate of Perceived Exertion Scale will be used to monitor effort and scale the intensity of the workout [47]. To promote post-exercise muscle protein synthesis, a nutritional supplement (200ml pre-prepared ‘protein shake’, Fresubin) which consists of 20g of protein will be offered immediately post exercise. The ‘Park Walk’ will focus on the aerobic component of the intervention, using open green space to maximise physical and mental health outcomes. It will be a flexibly arranged 20–30-minute self-paced group or one-to-one walk. To build sustainability beyond the ten-week programme brief health promoting and physical activity educational interventions will be included in the exercise class setting to empower people to engage in unsupervised exercise following the study. As per routine procedure in the centre, which incorporates frequent reminders regarding upcoming appointments or events, phone messages will be incorporated to remind participants of the weekly schedule.

**Table 3 pone.0300412.t003:** Exercise circuit.

Core exercise	Initial Intensity	Progression/Adaptations*
Sit to stand or squats or lunges	2 sets 10–15 reps	3 sets of 15 reps use of weights/ball/upper limbs
‘Bicep cursl’-Elbow Bends	2 sets 10–15 reps	3 sets of 15 reps use of weights/theraband
Step-ups	2 sets 10–15 reps	3 sets of 15 reps Vary height of step; use of weights & upper limbs
Arm elevations or boxing activity with research assistant	2 sets 10–15 reps	3 sets of 15 reps use of weights or boxing gloves/pads
‘Penguin waddle’-alternate hip abduction in standing (unsupported if able)	2 sets 10–15 reps	3 sets of 15 reps additional upper limb abduction and elevation; movement with 360° turns
Scapular retractions	2 sets 10–15 reps	3 sets of 15 reps Weights/theraband
Aerobic, balance and co-ordination activity	5 mins	Exercise bike, ladders, hurdles (running forward, sidewards, add in high knees or heel kicks), skipping ropes, end of session fun activity.
Core set (mat work) Women’s health focussed exercises	5 mins	Deep breathing exercise, pelvic floor exercises; pelvic tilts, bridging, all 4’s set with upper/lower limb extensions.

Adaptations: exercises performed in standing, individualised and progressed for each participant by research physiotherapist modified to chair-based exercise for those with mobility limitations.

Progression: 2–3 sets of 10–15 repetitions completed at each session; beyond that, low resistance weights (1.1kg-4.5kg), theraband or increased step height introduced to achieve a strengthening effect.

Each session will commence with a warm-up and will be completed with a cool down and stretch of the major muscle groups.

#### Qualitative data

Following the intervention one-to-one in-person semi-structured exit interviews will be conducted to enable participants to share their feedback and express their views, in order to enhance the understanding of behaviours, adherence and retention challenges and to provide insights for future programmes in this area [48] (S2 File). In order to gain a deep understanding of a complex phenomenon, multiple perspectives will be sought using purposive sampling, selecting participants who provided informed consent and completed at a minimum the initial pre-intervention evaluation as well as key stakeholders involved in service provision to women who attend the low threshold services in MQI. Data from 20 participants will be sought. The interviews will be audio-recorded in a private room in Jane’s Place, by the lead researcher FK, using a Philips Dictaphone (DVT2050). Data will be immediately transferred to Sharepoint, a secure cloud-based system and then transcribed verbatim by FK. Member checking will be utilised. FK has knowledge and experience of quantitative and qualitative research methodology.

Braun and Clarke’s reflexive thematic analysis will be used to interpret the qualitative data [49, 50]. An inductive approach will be utilised, guided by the 6-step framework. This will include 1) familiarisation with the data, 2) coding, 3) generating themes, 4) reviewing themes, 5) defining themes, and 6) writing up. Qualitative data will be coded manually by FK and software will not be used. An external validator will assist in coding, theme generation, review, and definition. FK will conduct the narrative which will include integration with the quantitative data.

Using a hybrid design, the quantitative and qualitative data will be collected sequentially, as described, and the results will be analysed and presented separately [51, 52].

#### Sample size

A sample size calculation was conducted on the statistical package R, based on an expected adherence of 60%, a minimal acceptable adherence of 45% and a power of 80%, which indicated that a target sample size of 68 would be required. Due to the novelty of this study, the challenges of recruitment in this ‘hard to reach’ population and the feasibility focus of this study, while 68 will be the recruitment target, a minimal of 24 will be sought [53].

## Data collection and management

### Analytic plan

All data will be pseudonymised at point of entry into excel spreadsheets and then transferred into IBM SPSS V28 for analysis. For quantitative data, nominal or ordinal variables will be reported as frequencies and percentages. Continuous variables will be summarised as mean and standard deviation if normally distributed and median and inter-quartile range if non-normally distributed. Data will be tested for normality using the Kolmogorov–Smirnov/Shapiro Wilk test and will be compared across timepoints using the general linear model procedure (normally distributed data) and the Friedman’s test (non-normally distributed data). Chi-squared t-tests will be used where appropriate and some data may be categorised to investigate relationships between variables. Exploratory regression models will be developed to explore correlates and predictors of frailty and poor physical functioning. For the qualitative data, Braun and Clarke thematic analysis methodology will be employed to provide an in-depth analysis of the exit interview data [50]. A *p*-value of <0.05 will be considered significant. To account for multiple comparisons, we will apply a Bonferroni correction by dividing the significance level by the number of tests conducted.

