Health services for PEH frequently focus on crisis-based medical, nursing and addiction services, often with a gender-blind lens [18, 19]. High levels of stigma, shame and fear result in women accessing services even less and seeking help at breaking point with complex coinciding physical and mental health needs [20, 21]. Homelessness and substance use in women is inter-sectoral and may overlap with trauma, abuse, domestic and sexual violence and exploitation, and the needs of these women are complex and unique [22]. Pathways into homelessness are frequently different to that of men and require a different approach [23]. Internationally, gender-based services for women who are experiencing homelessness and addiction are lacking and services are mostly delivered in mixed gender settings [18, 19]. Women-specific services are recommended to increase safety, stability, wellbeing, and psychosocial functioning to respond meaningfully to the serious health and social care needs of women in this setting [24]. Gender specific and gender sensitive research is required to fill this knowledge gap [25].

Our prior research, the LEAP-I study demonstrated high retention (83% female v 42% males) with excellent engagement and feedback from its female participants, yet caution was observed around engaging in a mixed exercised programme with men [16]. Women have traditionally been underserved in research and policy, yet multiple sources cite women as the fastest growing homeless demographic [23]. No study has examined how targeted women-only exercise programmes with nutritional supplementation work in practice in this population.

The overall aim of this study is to evaluate the feasibility and impact of exercise with protein supplementation, delivered with a low threshold and trauma informed approach, on physical functioning and frailty outcomes in a group of (non-geriatric) women experiencing homelessness and addiction challenges, through the delivery of an exercise intervention, followed by qualitative interviews. The objectives are:

To evaluate recruitment, retention and adherence rates, and any adverse effects of the intervention.To evaluate pre- and post-intervention levels of physical function, nutritional and frailty status, pain, and general health status.To evaluate programme feedback and gain deeper insights into participants perspectives and experiences of the exercise intervention.

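### As plainly read, the normality check that picks the pre-post test looks at the measured values rather than each woman's change, which can cost power on some secondary outcomes (minor)

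*Protocol article*

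**What the plan says.** The Analytic plan uses one label, normally distributed or not, for two decisions.

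- Summary statistics: "Continuous variables will be summarised as mean and standard deviation if normally distributed and median and inter-quartile range if non-normally distributed".
- Choice of test: the data undergo a Kolmogorov–Smirnov or Shapiro-Wilk check and "will be compared across timepoints using the general linear model procedure (normally distributed data) and the Friedman’s test (non-normally distributed data").

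In the second sentence the same grammatical subject is both tested for normality and compared over time. The objectives in the Introduction set two assessments: "To evaluate pre- and post-intervention levels of physical function, nutritional and frailty status, pain, and general health status". The threshold is a p-"value of <0.05 will be considered significant", and for multiple comparisons "we will apply a Bonferroni correction by dividing the significance level by the number of tests conducted". The number of tests is not given.

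**The concern.** The question for a summary table is whether a variable is normal across women. The question for a paired comparison is whether the within-woman changes are normal. These are different conditions. Stable differences between women cancel in the change, so an outcome can be strongly skewed across a group aged 18-65 with very mixed health while its changes are close to normal. The reverse is also possible.

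A selector keyed to the measured values can therefore drop the general linear model for a reason unrelated to its validity. It also gives no answer when the pre values pass and the post values fail. At stake is power for the secondary pre-post comparisons of function, frailty, nutrition, pain and health status, which carry the impact part of the study's aim.

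**Working it through.** **1. The plan's own figure.** Inputs from the Sample size section: expected adherence 60%, minimum acceptable 45%, power 80%. One-sample proportion, normal approximation, one-sided 5% (assumed; sidedness is not stated):

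n = [(1.645·√(0.45·0.55) + 0.842·√(0.60·0.40)) / 0.15]² = [(0.818 + 0.412) / 0.15]² = 67.3, so 68. This reproduces the target; a two-sided 5% level would give 86. The target rests on adherence, and no pre-post test enters it.

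**2. What the paired model needs.** Write post = pre + D. With two timepoints the repeated-measures general linear model is the paired t-test, t = mean(D) / (s_D/√n), F = t². Only D enters, so only its distribution matters.

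**3. What Friedman's test becomes.** With two timepoints and no ties, its statistic is (n₊ − n₋)²/n, where n₊ and n₋ count women who rose and fell. That is the sign test. Take normal changes, two-sided 5%, and a true change that gives the t-test 80% power (an assumption: the protocol gives no effect size or SD for these outcomes).

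- N = 68: change 0.345 SD, P(D>0) = Φ(0.345) = 0.635. Reject if n₊ ≥ 43 or ≤ 25. Power 57%.
- N = 40: change 0.454 SD, P(D>0) = 0.675. Reject if n₊ ≥ 27 or ≤ 13. Power about 58%.
- N = 24: change 0.597 SD, P(D>0) = 0.725. Reject if n₊ ≥ 17 or ≤ 7. Power 67% with the chi-square p-value (true size 0.064), or 50% with the exact p-value (size 0.023).
- Large-sample check: Φ(2.80·√(2/π) − 1.96) = Φ(0.275) = 61%.

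So an outcome with normal changes that is sent to Friedman's test loses about 23 points at 68, 22 at 40, and 13 or 31 at 24.

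**4. How often the rule sends it there.** Simulation, 3000 trials per setting. Baseline is lognormal (log-SD 0.5), with SD 1.5 times the SD of change, so the pre-post correlation is 1.5/√(1.5² + 1) = 0.83. Changes are normal. Shapiro-Wilk is applied at 5%, and Friedman's test uses the chi-square p-value.

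| N | To Friedman, values checked (either timepoint) | To Friedman, changes checked | Power, values (either) | Power, changes | Loss, either | Loss, both must fail |
|---|---|---|---|---|---|---|
| 24 | 64% | 5% | 72% | 80% | 8 | about 3 |
| 40 | 85% | 5% | 59% | 78% | 19 | about 9 |
| 68 | 98% | 5% | 59% | 79% | 20 | about 13 |

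Pre and post values disagreed on normality in about 37-46% of trials. Repeat runs moved the powers by a few points.

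**5. Where the loss shrinks or reverses.**

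- Changes proportional to level: about 3 to 5 points; other parameter choices gave up to 7.
- Bounded integer 0-10 score: under 1 point, and 3 points or fewer under other parameters. The changes fail the normality check too, so both rules mostly end at Friedman's test.
- Timed score with an assumed 45 s ceiling and proportional change: 0 to 2 points.
- Baseline normal across women: about 1 point or less.
- Signed-rank test as the fallback instead of Friedman's: about 1 to 2 points.
- Heavy-tailed changes: at N = 24 Friedman's test had the higher power (94% v 85% for t with 3 df; 89% v 81% for Laplace).

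**6. Type I error.** Under the rule keyed to measured values it was 0.034 to 0.064 in simulation.

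**The case against.** The strongest reply is about the text. The article says only that data are tested. It does not say values, values per timepoint, differences or residuals, and an unseen analysis plan might specify the changes. That stands in part: the reading is the plain one, not an express statement. It does not dissolve the point. The article does state a selection rule, it gives the tested and the compared quantity one subject, and it uses the same label to choose the summary statistic. That label can only sensibly refer to the values.

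The second reply is about cause. With a signed-rank fallback the loss would be 1 to 2 points, so most of the power cost belongs to Friedman's test with two timepoints and not to the selector. This is correct.

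The third reply is about realism. Normal changes independent of level are a favourable case. Pain scored 0-10 cannot have normal changes, and the description of the outcome measures itself anticipates floor and ceiling effects. This also stands.

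A reader might go further and infer that the trial will lose about 20 points of power, that the loss always grows with recruitment, or that false positives are inflated. The documents do not support these. They give no SD, skew or effect size for any functional outcome. The gap closes with recruitment for bounded scores. The simulated type I error stays near 5%.

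**Conclusion.** The point holds as a minor one. On its plain reading, the plan lets the measured values settle a question that belongs to the within-woman changes, and it does not say what happens when the two timepoints disagree.

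For outcomes skewed across women but with near-normal changes, the avoidable loss is about 8 points at 24 women and about 20 at 40-68 if either timepoint triggers Friedman's test, or about 3 to 13 if both must be non-normal. It is about 3 to 5 points with proportional changes and almost none for bounded scores. These figures assume a true change that gives the paired general linear model about 80% power at a two-sided 5% level. With an assumed ten Bonferroni tests (level 0.005), an outcome with normal changes sent to Friedman's test at N = 68 would lose about 25 points.

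Only secondary outcomes are touched. The feasibility primary outcome and the target of 68 stand as they are.

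**What to change.** In the Analytic plan, separate the two uses of the normality check:

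- The distribution of a variable at each timepoint decides only how it is summarised.
- The pre-post test is chosen from the distribution of the within-woman changes (post minus pre; equivalently the model residuals).
- The mean or median change is reported with its 95% confidence interval.

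This also settles the case in which pre and post values disagree. The cost is a sentence or two in the plan and one derived variable per outcome, with no new data. The small downside is that some outcomes will be summarised by medians but tested with the general linear model, which needs a table footnote. The change does not alter the fallback: outcomes whose changes are non-normal still go to Friedman's test, which with two timepoints remains the sign test.

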#### Stakeholder engagement

Recommendations from the linked LEAP II trial [17] included health education and awareness workshops preceding exercise interventions to enhance health literacy, target lifestyle behavioural change and improve retention rates. Prior to the LEAP-W programme, a number of exercise workshops will be delivered for staff and service users in Jane’s Place. Feedback from this stakeholder engagement will inform the design of the intervention.

*Primary outcome*. The primary outcome is feasibility which will be measured by recruitment numbers, retention rate, adherence to the exercise programme and protein supplement, programme acceptability and adverse events (Table 1).

**Table 1 pone.0300412.t001:** Feasibility markers.

Primary Outcome: Feasibility	Method of reporting
Recruitment Numbers	Number of eligible consenting participants who completed the initial assessment
Retention rate Sub-group retention rate	Number of return visits and the frequency of attendance • *attending at least once/week for > 50% of the duration of the programme (regular attenders)* • *attending at least once/week for < 50% of the duration of the programme (sporadic attenders)* • *did not return following initial assessment (non-attenders)*. • *attendance by chronological age*, *and pre- and post-menopausal status*.
Adherence rate *(*to the exercise intervention)	Percentage of sessions adhered to/completed by participants
Adherence rate (to the nutritional supplement)	Percentage of participants who consumed the protein supplement drink
Adverse events	An unfavourable and unintended sign, symptom, or disease having been absent at baseline, or, if present at baseline, appears to worsen and is temporally associated with medical treatment or procedure, regardless of the attribution [26]
Programme Acceptability	Participant feedback provided by Exit Interviews.

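### The named pre-post tests use only women assessed at every timepoint, while the aim speaks of impact without that limit

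*Protocol article*

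**What the plan says.** - **Test.** In the Analytic plan, normally distributed outcomes "will be compared across timepoints using the general linear model procedure (normally distributed data"; Friedman's test serves non-normal data. Data are "transferred into IBM SPSS V28 for analysis".
- **Who is enrolled.** Table 1 defines recruitment as "Number of eligible consenting participants who completed the initial assessment", so every enrolled woman has a baseline.
- **Who may be lost.** Table 1 has a class for women who "did not return following initial assessment (non-attenders". The Introduction reports that the linked LEAP-I study "demonstrated high retention (83% female v 42% males".
- **What is claimed.** The overall aim in the Introduction is to "evaluate the feasibility and impact of exercise with protein supplementation" on physical functioning and frailty in a group of women. The matching objective is more modest: "To evaluate pre- and post-intervention levels of physical function, nutritional and frailty status, pain, and general health status".
- **Later contact.** Under Qualitative data, exit interviews are open to women who "completed at a minimum the initial pre-intervention evaluation", so low attendance does not exclude a woman.

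**The concern.** Friedman's test needs complete blocks, and the SPSS repeated-measures general linear model deletes any case with a missing timepoint. Restriction to women with both assessments is thus a consequence of the methods named, even though the article does not spell it out. The baseline values of women who are not reassessed are collected but play no part in the change estimate.

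If the women who come back differ at baseline from those who do not, the completer change differs from the change in the whole group. A single-arm study has no comparison group in which selective return would show up. The result would then be read as the impact of the programme in these women, which is wider than what the analysis estimates.

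**Working it through.** **1. The plan's own figure.** The Sample size section gives 68, from 60% expected and 45% minimal acceptable adherence at 80% power. For a one-sample proportion:

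n = [(1.645·√(0.45·0.55) + 0.842·√(0.60·0.40)) / 0.15]² = 67.3, so 68.

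This reproduces with a one-sided 5% level (two-sided gives 86). It is sized on adherence, not on pre-post change.

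**2. How many women would have paired data.** The share reassessed is not given. As an assumed range I take 83% (LEAP-I retention of women, whose definition the article does not give) and 60% (the expected adherence, borrowed only as a plausible value).

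| Enrolled | 83% reassessed | 60% reassessed |
|---|---|---|
| 68 (target) | 56 | 41 |
| 24 (minimum) | 20 | 14 |

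**3. Return depends on baseline.** Assume equal SDs before and after, pre-post correlation ρ = 0.7, and return governed by a normal variable correlated c with baseline. Then:

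bias of completer change = (ρ − 1) · c · φ(z)/r

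where r is the share returning and φ(z)/r is 0.305 at r = 0.83 and 0.644 at r = 0.60.

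| r | c | Bias (SD of the outcome) |
|---|---|---|
| 0.83 | 0.3 | −0.3 · 0.3 · 0.305 = −0.03 |
| 0.83 | 0.5 | −0.3 · 0.5 · 0.305 = −0.05 |
| 0.60 | 0.3 | −0.3 · 0.3 · 0.644 = −0.06 |
| 0.60 | 0.5 | −0.3 · 0.5 · 0.644 = −0.10 |

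A simulation with N = 68, 60% return and a true change of 0.30 SD agrees. The completer mean was 0.24 at c = 0.3 and 0.20 at c = 0.5, while the likelihood estimate from all baselines and available post values was 0.30 both times. Standard errors were 0.121 against 0.121 at c = 0.3, and 0.121 against 0.126 at c = 0.5. With c = 0 both methods gave 0.30.

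The sign follows c. On a scale where higher is better, if the fitter women return, the completer gain is understated; if the frailer return, it is overstated.

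**4. Return depends on the change itself.** With N = 68, no mean change among all enrolled, and a completers-only paired t-test at two-sided 5%:

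| Correlation of return with change (assumed) | Bias in SD of change, 83% / 60% return | Type I error, 83% / 60% return |
|---|---|---|
| 0 | 0 / 0 | 0.05 / 0.05 |
| 0.3 | 0.09 / 0.19 | 0.11 / 0.23 |
| 0.5 | 0.15 / 0.32 | 0.22 / 0.58 |

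**5. Does the mixed model help in that case?** Suppose returners gain 0.5 SD and the others nothing. The all-enrolled change is 0.83 · 0.5 = 0.415 or 0.60 · 0.5 = 0.30 SD. With N = 68 or 24 and pre-post correlations of 0.5 to 0.85, the likelihood estimate stayed at 0.50, the same as the completer result.

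**6. Precision.** A paired t-test with 80% power at an unadjusted two-sided 5% detects 0.60 SD with 24 pairs and 0.81 SD with 14. The mixed model does not recover that loss: with 24 enrolled and 14 returning, and return unrelated to baseline, it reduced the standard error by at most about 4%.

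**The case against.** The strongest reply is that a condensed article commonly leaves the analysis set and missing-data handling to an analysis plan, so silence on them is no fault. That stands, but the point does not rest on silence: the tests are named, and they exclude women without a post value whatever else a fuller plan adds.

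Four further objections stand and limit the point.

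- A reader might infer that the change is to be labelled as impact for all enrolled. No section says so. The aim speaks of a group of women, and the objective only of levels before and after.
- Attendance is not reassessment. Table 1 classifies return visits and frequency of attendance. Sporadic attenders may well be reassessed, and nothing restricts the post battery to regular attenders.
- The documents do not show that women who leave are frailer. Even if they are, frailer women may have more room to improve, so the direction of bias is open.
- The outcomes are secondary in a feasibility study. Retention is reported as a primary outcome, so readers will see how many women stayed.

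**Conclusion.** The point holds as a minor to moderate one on secondary outcomes. The named methods estimate change among women assessed at every timepoint, and the aim does not carry that limit. Under baseline-dependent return the completer estimate is off by about 0.03 to 0.05 SD at 83% return and 0.06 to 0.10 SD at 60%, in either direction. These sizes rest on assumed return shares and correlations. With return unrelated to baseline and to change, the bias is nil.

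Two stronger readings are tempting and not supported. The first is that the reported change is 1.2 to 1.7 times too large. Those factors are just 1/0.83 and 1/0.60; they require non-returners to change by exactly zero, and the mixed model would not correct them. The second is that the choice of test costs precision. The rise from 0.60 to 0.81 SD comes from missing post values, which no model on the same data restores.

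**What to change.** 1. Analyse continuous outcomes with a linear mixed model (SPSS MIXED, in the software already named), using all baseline and all available post values. Keep the completer analysis as sensitivity. Where Friedman's test is retained, state that it covers only women assessed at every timepoint.
2. Offer the post battery to every enrolled woman who can be reached, whatever her attendance. The exit interview is one such contact, but only 20 are sought and stakeholders are also sampled, so it will not reach everyone.
3. Report the number with paired data for each outcome, and a baseline table of women reassessed against women not reassessed.
4. Word the result as observed pre-post change and not as impact.

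The cost is a few sentences in the Analytic plan and some extra follow-up contact. The model relies on missing at random, recovers almost no precision, and does not correct for return that depends on unobserved change. Step 2 is the only one that addresses those last two limits.
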